### NIRS monitoring data

Each NIRS oximetry probe will continually produce 4 streams of data: StO_2_; HbT; HbO_2_; and HbD with values recorded every 4 seconds. Standard clinical monitoring will be recorded at the same time as the NIRS oximetry data captured by the EQUANOX device. This will include peripheral pulse oximetry, end-tidal capnography (where indicated for patient care), heart rate and non-invasive blood pressure and will be updated on the record every ten seconds. This general observations data will be time-matched to the NIRS oximetry monitoring data to allow direct comparisons of values in data analysis, particularly in the signals analysis related to Aim 1. Clinically relevant information such as any degree of prehospital hypoxia or hypotension will therefore be time-matched to the NIRS oximetry monitoring data.

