### Early phase outcome data

Patient outcome and follow-up data related to initial findings and hospital stay will be obtained from the hospital by the trial research nurse at a time beyond 30 days from the injury and include: (1) Injury Severity Score (ISS) and Abbreviated Injury Scores (AIS) for each body region [27,28]; (2) injuries identified on independent review of first cerebral imaging by computerised tomography (CT) or magnetic resonance imaging (MRI); (3) 24 hour and 30 day mortality; (4) survival to hospital discharge; and, (5) length of intensive care unit (ICU) stay including number of ventilator days.

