### Subgroups for analysis and reporting

Some patients, particularly those with more severe injuries and those of a different age, are more likely to have monitor findings indicating strong associations with outcomes and are therefore of particular interest. Subgroup analysis will be undertaken on patients with severe TBI (first GCS ≤ 12 and Abbreviated Injury Score (Head) ≥ 3), severe traumatic injury (ISS > 15), and paediatric patients (age < 16 years).

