#### Statistical analysis for aim 2: associations of nirs tissue oximetry with acute phase outcomes

The area under the curve for cerebral oximetry value ≤ 45% (minutes x desaturation points ≤ 45%) will be used as an independent variable for statistical analyses as described previously [34]. Patients with one or more episodes of cerebral oximetry value ≤ 45% for 1 minute will be classified as experiencing a decline in cerebral oxygen saturation.

We will define 3 NIRS cerebral oximetry patient groups:NIRS 1 (cerebral oximetry values remain > 45% i.e. area under the curve = 0 min%).NIRS 2 (cerebral oximetry values ≤ 45% for > 0 min up to the median area under the curve for cerebral oximetry value ≤ 45% to be determined).NIRS 3 (cerebral oximetry values ≤ 45% for more than the median area under the curve for cerebral oximetry value ≤ 45% to be determined).

The total duration (minutes) of StO_2_ ≤ 45%, longest duration (minutes)

StO_2_ ≤ 45%, minimum and average StO_2_ will be derived for each patient. These variables will be compared between NIRS 1, NIRS 2 and NIRS 3 groups using Kruskal-Wallis analysis of variance to check the validity of this grouping.

A chi-square test will be used to assess the association between cerebral oximetry values by comparing patients in each of the above groups in their association with the following injury patterns on cerebral imaging: no intracranial pathology, intracerebral lesions present, subdural haematoma, extradural haematoma, traumatic subarachnoid haemorrhage and diffuse injury. The same analysis will also be repeated to establish associations with 24 hour and 30-day mortality and survival to discharge.

In the multivariate analysis, an ordinal logistic regression under a proportional odds model with NIRS 1 as the reference group will be used with the six types of injury on cerebral imaging listed above included as an independent variable after adjusting for ISS, age, sex and other covariates (mean arterial pressure, first recorded GCS, peripheral oximetry, end-tidal CO_2_, HbT) in a stepwise fashion. A score test will be used to verify the proportional odds assumption in the final model. The unadjusted and adjusted odds ratios and 95% confidence intervals will be reported. Significance will be set at P < 0.05.

### Outcomes for aim 2

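### Aim 2 adjusts lesion type for a total ISS that contains the same head injury, and puts a selectively measured end-tidal CO2 into a stepwise model

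*Protocol article*

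**What the plan says.** The protocol article's section Statistical analysis for aim 2 sets up a proportional odds model. NIRS group is the ordered response with NIRS 1 as reference, "with the six types of injury on cerebral imaging listed above included as an independent variable". One of the six imaging categories is a scan without intracranial pathology. The model is fitted "after adjusting for ISS, age, sex and other covariates", the latter listed as mean arterial pressure, "first recorded GCS, peripheral oximetry, end-tidal CO_2_, HbT) in a stepwise fashion". Unadjusted and adjusted odds ratios with 95% confidence intervals are to be reported, with significance at P < 0.05.

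Three other places bear on these covariates:

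- Early phase outcome data: the research nurse obtains "Injury Severity Score (ISS) and Abbreviated Injury Scores (AIS) for each body region" from the hospital, "at a time beyond 30 days from the injury".
- Subgroups for analysis and reporting: severe TBI is defined partly by "Abbreviated Injury Score (Head) ≥ 3", so the head is one of the scored regions. No extracranial version of ISS is defined anywhere.
- NIRS monitoring data: the clinical signals recorded alongside NIRS include "end-tidal capnography (where indicated for patient care").

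Statistical analysis for aim 3 reuses the same modelling approach.

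**The concern.** Outcomes for aim 2 gives the target: how cerebral oximetry relates to the kind of brain injury. Three features of the adjusted model work against a clear answer.

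- **Total ISS.** The lesion enters once as the explanatory variable and again inside a covariate. At equal total ISS, a patient whose points come from the head must have less injury elsewhere than a patient with a clean scan. The adjusted odds ratio then mixes a lesion effect with a trade-off against extracranial injury.
- **End-tidal CO2.** Whether it is measured depends on clinical state. If patients without a value drop out of the fit, those who remain are selected on that state. Patients with a clean scan may plausibly lose most, and they form the natural comparison category.
- **Stepwise selection.** Intervals and P values computed as if the final model had been fixed beforehand are too confident.

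**Working it through.** **1. The plan's own figure.** Power analysis gives 242 severe-TBI subjects for 90% power at a correlation of 0.22 (two-sided 0.05), including 29 failed monitoring attempts. By Fisher's z, n = ((1.960 + 1.282)/atanh(0.22))² + 3 = 213.06, and 213 + 29 = 242. The figure reproduces, so this point does not rest on a wrong sample size. It supplies 213 as the number of evaluable severe-TBI subjects.

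**2. Head content of ISS.** Assumption: ISS is the sum of squared AIS over the three worst body regions. The article does not spell this out.

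- Head AIS 3, the minimum in the severe-TBI definition: 3² = 9 points from the head, whenever the head is among the regions counted.
- Isolated head AIS 4: 4² = 16, all from the head, and enough alone to pass the article's ISS > 15 threshold for severe traumatic injury.
- Head AIS 5 with chest AIS 3: 25 + 9 = 34, of which 25/34 = 74% is head.

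These figures show overlap in content. They do not measure bias.

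**3. What the overlap can do to an odds ratio.** Illustration with 200,000 simulated patients; every distribution is assumed.

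- Head AIS 0/2/3/4/5 with probabilities 0.5/0.2/0.1/0.1/0.1.
- First other region AIS 0–4 with probabilities 0.2/0.25/0.25/0.2/0.1; second other region AIS 0–3 with 0.4/0.3/0.2/0.1; all regions drawn independently.
- Lesion = head AIS ≥ 3; ISS = sum of the three squares.
- Binary low-oximetry response with logit = −2 + 0.3 × head AIS + 0.025 × (sum of the two extracranial squares).

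The correlation of ISS with lesion was 0.72, a variance inflation of 1/(1 − 0.72²) ≈ 2.1.

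| Adjustment | Lesion odds ratio |
|---|---|
| none | 2.79 |
| total ISS | 1.62 |
| extracranial score | 2.80 |

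This simplifies the plan: one lesion indicator instead of six types, and a binary instead of a three-level response. The extracranial result sits close to the unadjusted one because head and other injuries were drawn independently. The illustration shows that the mechanism can be material; it does not estimate the effect in this cohort.

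**4. End-tidal CO2 under complete-case fitting.** The share f with capnography is not in the document, so a range is assumed. Retained n = 213 × f; standard errors grow by 1/√f; power is for a correlation of 0.22, borrowed from the Aim 1 calculation as a yardstick only.

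| f (assumed) | n | SE factor | Power |
|---|---|---|---|
| 1.0 | 213 | 1.00 | 90% |
| 0.7 | 149 | 1.20 | 77% |
| 0.5 | 106 | 1.41 | 62% |
| 0.3 | 64 | 1.83 | 42% |

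At f = 0.9 the figures are 192 patients and 87% power. Severe-TBI patients are plausibly those most likely to have capnography, so the lower rows may be pessimistic for them. The denominator is also unclear: Power analysis sizes Aims 2 and 3 on the same number of subjects, while 1210 are recruited and severe TBI is listed as a subgroup.

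**5. Stepwise selection.** No arithmetic applies. The article reports conventional 95% intervals from a selected model. The planned bootstrap on 1000 samples is described as internal validation; nothing says that selection is repeated in each sample or that intervals are corrected.

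**The case against.** The strongest reply has four parts.

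- **Total ISS can be a legitimate adjuster.** Asking whether lesion type matters beyond overall severity is a valid question, and ISS captures extracranial injury, a real confounder. This stands in part: adjustment does not condition on the lesion itself, and a pull towards the null is a risk, not an established result. But one imaging category is the absence of a lesion, so for that contrast total ISS carries much of what is being compared. An extracranial score handles the confounder without the overlap.
- **Restriction to patients with capnography is not in the document.** A reader might infer that the adjusted results are confined to them. The article states no deletion rule, and missing-data handling may sit in an analysis plan not shown. Nor is imputation ruled out: a patient without capnography has an unmeasured CO2, not an undefined one, and likely drivers of measurement (first GCS, ventilation, intubation) are recorded. This stands, and the point is conditional on complete-case fitting.
- **The covariate set is not fixed.** A reader might take the list as a final adjustment set. It is a list of named candidates, and end-tidal CO2 may not be selected. Under complete-case fitting, however, an unselected candidate still determines who is analysed, because the models being compared need a common sample. If the wording means entry in planned blocks, the selection criticism falls away and CO2 affects only the later block.
- **Unadjusted odds ratios, chi-square tests and bootstrap validation are planned.** They are, and the first two are untouched by this point. None of them repairs the adjusted analysis.

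**Conclusion.** The point holds as a risk to the adjusted Aim 2 results. That total ISS overlaps with lesion type follows from the article's listing of regional AIS, head included, together with the usual construction of ISS. The size of any over-adjustment depends on AIS distributions the article does not give, and the fall from 2.79 to 1.62 is an illustration only. That end-tidal CO2 is measured selectively and is nevertheless a candidate covariate is stated outright; the loss of patients follows only if incomplete cases are dropped, and its extent is unknown. The criticism of intervals and P values applies if stepwise means data-driven selection, which is the ordinary reading. The authors should amend the analysis wording; the study's data collection is not in question.

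**What to change.** In the Aim 2 model:

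1. Replace total ISS with extracranial severity, either the highest non-head AIS or ISS computed without the head region. Keep the total-ISS model as a sensitivity analysis if wanted.
2. Enter the covariates as one prespecified set instead of stepwise.
3. Leave end-tidal CO2 out of the main model and use it only in a secondary model in patients with capnography, labelled as such.

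Regional AIS and the other covariates are already collected, so this changes analysis wording only. The small downside is that the main model loses direct CO2 adjustment.

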### Power analysis

Pre-existing datasets showing the relationship between prehospital NIRS oximetry values and patient injury outcomes in the context of TBI are lacking. To answer Aim 1, a sample size of 242 subjects with severe TBI will provide 90% power to detect correlation of 0.22 or higher [33] in a 2-sided 0.05 level test of the null hypothesis of no correlation between NIRS cerebral oximetry values and admission Glasgow Coma Score (GCS) adjusting for 29 (approximately 12%) unsuccessful NIRS monitoring data collection attempts (25) in a time series based regression analysis. CareFlight’s historical mission database indicates 1210 total recruits will be required to incorporate 242 subjects with severe TBI.

To address Aims 2 and 3, the same number of subjects will be enough to show an incidence of EGOS 4 at six months post-injury of 56% (95%CI 49% to 63%) and demonstrate a clinically important change in EGOS of 1 point associated with NIRS cerebral oximetry value at 80% power to detect a Cochrane-Armitage test for trend in EGOS groups (30% deceased, 20% poor neurological outcome and 50% good neurological outcome) at significance level of 0.05. The expected proportion of EGOS groups have been taken from the subject characteristics from the Head Injury Retrieval Trial [data under analysis] [29].

As for validation of the model for Aims 2 and 3, we will internally validate the models using bootstrapping methods on 1000 samples.

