#### Statistical analysis for aim 3: associations with long-term outcomes

Utilising the same groupings for NIRS tissue oximetry (NIRS 1 through 3), associations with EGOS (grouped into EGOS < 2, 2–4 and 5–8), GOS and CANS will be tested with the same multivariate analyses and ordinal logistic regression approach described above. This will include adjustment for ISS, age, sex and other covariates. For validation of the model for Aims 2 and 3, we will internally validate the models using bootstrapping methods on 1000 samples. All data analysis will be performed using SPSS version 21 and STATA 13.1 software (StataCorp, College Station, TX).

### Outcomes for aim 3

This analysis will establish simple associations between NIRS cerebral oximetry values and the subsequent long-term functional recovery of patients with TBI. This would potentially allow early identification of patients with more severe injuries to optimise early intervention and engagement of rehabilitation services.

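### Aims 2 and 3 choose confounders stepwise and then test at P < 0.05; if the choice is data-driven, the adjusted associations reject too often, by an amount the protocol does not fix

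*Protocol article*

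**What the plan says.** The Aim 2 statistical analysis section of the protocol article specifies a proportional-odds model with NIRS 1 as the reference group. The six imaging injury types enter as an independent variable. Adjustment is for ISS, age and sex and for five further covariates: mean arterial pressure, first recorded GCS, "peripheral oximetry, end-tidal CO_2_, HbT) in a stepwise fashion". Proportional odds is then checked in the model that results. The section goes on: "The unadjusted and adjusted odds ratios and 95% confidence intervals will be reported. Significance will be set at P < 0.05".

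The Aim 3 section applies the same multivariate approach to EGOS (in three groups), GOS and CANS, and adds: "This will include adjustment for ISS, age, sex and other covariates". The models for both aims are to be validated internally on 1000 bootstrap samples.

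The article gives no entry or removal threshold, no list of forced terms, and no statement that selection is repeated in each bootstrap sample.

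**The concern.** Both aims are about association, so the adjusted odds ratio and its P value are the result. A stepwise rule keeps a covariate for its own significance in the model, not for how much it confounds the association of interest. In a sample of a few hundred, a real confounder of moderate strength often misses its threshold and is removed. Its effect is then partly credited to whatever term is being tested.

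The protocol's own reasoning makes this plausible. The Background names hypoxia and low blood pressure as causes of further brain damage. The Discussion cites a small study linking longer time at low StO2 with lower cerebral perfusion pressure and with mortality. Peripheral oximetry and mean arterial pressure may therefore be tied to both the NIRS values and the outcome, yet both are in the list open to selection.

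At stake is whether a significant adjusted association reflects cerebral oximetry or residual confounding. The Discussion looks ahead to studies in which interventions are guided by oximetry, so a spurious association would matter.

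**Working it through.** **Inputs from the protocol article**

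- Test level for the Aim 2 and 3 models: "Significance will be set at P < 0.05".
- Power analysis, Aim 1: "a sample size of 242 subjects with severe TBI will provide 90% power", with "power to detect correlation of 0.22 or higher [33] in a 2-sided 0.05 level test".
- Failed recordings: "adjusting for 29 (approximately 12%) unsuccessful NIRS monitoring data collection attempts", so 242 − 29 = 213 evaluable.
- Whole cohort: "1210 total recruits will be required to incorporate 242 subjects with severe TBI". If the same 12% fail (an assumption), 1210 × 0.88 ≈ 1065 are evaluable.
- EGOS groups: 30/20/50%. Candidate covariates: eight.

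**Step 1: reproduce the plan's own figure.** By Fisher's z, n = ((1.960 + 1.282)/atanh(0.22))² + 3 = (3.2415/0.22366)² + 3 = 213.06. Adding 29 gives 242, as stated (243 if 213.06 is rounded up first).

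**Step 2: which n applies to Aims 2 and 3?** The Power analysis says the same number of subjects serves these aims and gives 56% with a 95% CI of 49% to 63%. Using 0.56 ± 1.96 × √(0.56 × 0.44/n):

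- n = 213: 49.3% to 62.7%
- n = 242: 49.7% to 62.3%
- n = 1065: 53.0% to 59.0%

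Only 213 rounds to the stated interval, so 213 is the planning basis. The whole cohort remains a possible analysis set.

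**Step 3: simulate the type I error of the tested term.** The data come from a three-category proportional-odds model in which the tested term has no effect given all eight covariates. The tested term is always kept in the model.

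Assumed, not from the documents: pairwise covariate correlation 0.2; covariate effects of 0.15 or 0.3 log-odds per SD (plus one mixed 0.6/0.15 pattern in some cells); correlation r between each covariate and the tested term of 0.2 to 0.4; NIRS groups 50/25/25%. There were 400 to 1500 replicates per cell, so the Monte Carlo error is about 0.005 to 0.02.

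| Setting | r = 0.2 | r = 0.3 | r = 0.4 |
|---|---|---|---|
| Aim 3, n = 213, all eight kept | 0.052–0.053 | 0.052–0.070 | 0.050–0.062 |
| Aim 3, n = 213, backward removal at 0.05, all selectable | 0.063–0.077 | 0.080–0.117 | 0.153–0.215 |
| Same, removal at 0.10 | 0.061–0.071 | 0.071–0.105 | 0.105–0.172 |
| Aim 3, n = 213, ISS, age and sex forced, removal at 0.05 or 0.10 | 0.060–0.069 | 0.070–0.089 | 0.083–0.110 |
| Aim 3, n = 1065, removal at 0.05, all selectable | 0.050–0.064 | 0.050–0.064 | 0.052–0.116 |
| Aim 2 (NIRS group as response), n = 213, all eight kept | 0.040–0.043 | 0.046–0.049 | 0.053–0.057 |
| Aim 2, n = 213, removal at 0.05, all selectable | 0.061–0.063 | 0.094–0.101 | 0.151–0.193 |
| Aim 2, n = 213, ISS, age and sex forced, removal at 0.05 | 0.054–0.059 | 0.064–0.081 | 0.091–0.107 |

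Forward selection at 0.05 gave the same as backward removal where it was run (0.112 at r = 0.3 and 0.215 at r = 0.4). At r = 0 there was no inflation (0.049 and 0.054).

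**Step 4: express as multiples of 0.05.** The largest value is 0.215/0.05 = 4.3. With ISS, age and sex forced, the largest is 0.110/0.05 = 2.2. At n = 1065 one weak-effect cell reaches 0.116/0.05 = 2.3; the others lie between 1.0 and 1.3.

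**Step 5: does the bootstrap help?** As worded it validates the models internally. Even if selection were repeated in every resample, that would not put an omitted confounder back into the reported model.

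**The case against.** - **Stepwise may not mean data-driven.** It could mean adding pre-set blocks with nothing removed, and the model tested for proportional odds would then be the last block. On that reading the problem disappears. The wording does not exclude it, but the ordinary meaning of stepwise adjustment leading to a final model is selection.
- **Missing thresholds are SAP detail.** That stands: their absence from an article is no finding. The point rests on the method that the article does name.
- **ISS, age and sex may be forced.** The Aim 3 wording supports this, and it roughly halves the worst case. Mean arterial pressure, first GCS and peripheral oximetry would still be selectable.
- **The analysis set may be the whole cohort.** Eligibility covers transported trauma patients generally, severe TBI is listed as a subgroup, and the imaging categories include absence of intracranial pathology. At n = 1065 inflation is near 1 in most scenarios. That stands as a limit on size, although the stated interval points to 213.
- **Aim 2 does not test a NIRS effect.** A reader might infer that it does. As written, NIRS group is the response and injury type the tested term. The selection problem is the same in kind.
- **Keeping all eight covariates is not free.** The NIRS monitoring data section records capnography only when care calls for it, and HbT comes from the same probe as StO2. Both points stand and shape the fix.
- **Unadjusted odds ratios are also reported, and Aim 3 claims only simple associations.** Both are true, but the adjusted estimates are still reported and judged at 0.05.

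**Conclusion.** The point holds in a conditional form and is a cheap improvement. If stepwise means data-driven selection, the adjusted P values in Aims 2 and 3 are optimistic, because confounders can be dropped on their own P values and the test takes no account of the selection.

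A reader might infer that false positives run at two to four times the nominal rate. The documents do not support that: they give no correlations, effect sizes or removal rules. Over the assumed ranges the factor is about 1 to 4, often below 2, and near 4 only in the most extreme cell. The equal-effect cells also let all eight covariates act in the same direction, which favours the concern. A reader might also infer that the confidence intervals are too narrow by a known amount, but interval width and coverage were not computed.

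The finding that does not depend on the assumed ranges is the contrast: with the covariates fixed and kept, type I error stayed at about 0.04 to 0.07 in every scenario.

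**What to change.** In the Aim 2 statistical analysis section, and by reference in the Aim 3 section, replace the stepwise wording with text such as: *The adjusted model contains ISS, age, sex, mean arterial pressure, first recorded GCS and peripheral oximetry. All are retained whatever their P values, and no data-driven selection is done. Adjusted odds ratios are reported from this model.*

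Add end-tidal CO2 and HbT in a pre-specified sensitivity model, or include end-tidal CO2 in the main model with a pre-specified missing-data method. Forcing end-tidal CO2 in without such a method would drop patients who had no capnography. Adjusting for HbT is not plainly confounder control, since it is an output of the same probe.

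The simulation kept all eight covariates. With the six-covariate set, the test answers the question of association given those six, and the sensitivity model shows whether the other two matter.

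The cost is a short text change before analysis, a slightly wider confidence interval and one extra sensitivity analysis. If block entry was always intended, the same wording settles it.
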